#### Adherence and fidelity

Adherence (the number of performed versus prescribed training sessions) and fidelity (intensity and dose of performed *versus* prescribed exercise) to the exercise intervention will be monitored using a heart rate monitor (Polar Pacer^©^) and an online training diary (Coachbox). This training diary will offer prerecorded videos and pictures, periodized training volume, and personalized training intensities based on participants’ CPET results. If a training cessation of at least 7 days is required, participants will be asked to resume their training regimen at the level it was interrupted before the required training stop.

### Study outcomes

Outcome parameters will be assessed at five different timepoints: 3 months post-transplant (T1, baseline), 6 months post-transplant (T2), 9 months post-transplant (T3), 1 year post-transplant (T4), and 2 years post-transplant (T5). Figure 6 schematically presents the participant timeline and study outcomes measured per timepoint.

**Figure 6: fig6:**
[figure not shown]
Schematic overview of the participant timeline and study outcomes measured per timepoint.

Study procedures will take place at specialized laboratories of both University Hospitals Leuven and Ghent University Hospital, according to prespecified standard operating procedures. For different time points and centres, the order of examinations will be similar, starting with blood sampling, body morphology, and CV tests, all conducted in a fasting state (*cf. infra*). Subsequently, participants will be instructed to take their medication and consume a light breakfast standardized to the participants’ preferences and repeated during follow-up testing. Following this, further examinations will include: motor fitness, cardiorespiratory fitness, musculoskeletal fitness, and the completion of the questionnaires in presence of a member of the research team covering self-reported physical activity, safety, infections, QoL, implementation outcomes, and cost-effectiveness. Immediately after completion of the test day, participants will be requested to start wearing the Actigraph wGT3X-BT accelerometer for seven consecutive days.

All participants will be instructed to maintain an overnight fast (>6 hours) and refrain from caffeine, alcohol, and medication (>12 hours) until the fasting tests have been conducted. Participants will be instructed to refrain from moderate and high-intensity exercise two days prior to each testing day, to minimize acute physical activity-induced interference on the outcome measures.

#### Primary outcome: peak oxygen consumption

A cardiopulmonary exercise test (CPET) will be performed on a cycle ergometer (Ergoline 900, Bitz, Germany) using an incremental ramp protocol [55]. The test will begin with a 3-minute rest period, followed by a series of 10-, 15, or 20-W increments per minute until the participant reaches exhaustion or experiences medical signs or symptoms requiring the test to be stopped. Heart rate will be continuously monitored with a 12-lead ECG, and respiratory data will continuously be measured through breath-by-breath analysis (Oxycon Pro, Jaeger, CareFusion, Germany). Blood pressure will be measured at rest and every 2 minutes during the test. The highest 30-second average of oxygen consumption at the end of the test, defined as VO_2_peak, will be considered the main outcome of the test. Submaximal ventilatory thresholds during a CPET will be determined using a combination of methods [56]. The first ventilatory threshold will be identified by the breakpoint of linearity between minute ventilation and oxygen consumption, the breakpoint of linearity between carbon dioxide production and oxygen consumption (also known as the V-slope or gas exchange threshold), and the first increase in the ratio of minute ventilation to oxygen consumption over time. A second ventilatory threshold will be identified as the second breakpoint of linearity between minute ventilation and oxygen consumption or the first increase in the ratio of minute ventilation to carbon dioxide production over time. Two assessors will independently determine the ventilatory thresholds, and the mean of their values will be taken as the final value.

#### Secondary outcomes

##### Six-minute walking distance

Next to CPET-derived measurements, the six-minute walking test will be performed as a measure of functional cardiorespiratory fitness. During this test, the participant is asked to walk as far as possible within 6 minutes in a 30-m-long corridor, without running, and using walking aids as needed. Participants are motivated and informed about the remaining time in a standardized manner.

##### Endothelial function

Flow-mediated dilation of the brachial artery will be assessed using ultrasound (KU Leuven: UNEX EF, UNEX corporation, Nagoya, Japan; UGhent: ultrasound echo ‘GE Vivid 7’ with the Cardiovascular Suite) as a marker of endothelial function of the large blood vessels. Flow-mediated dilation, defined as the maximal diameter detected within three minutes post-occlusion in relation to the rest diameter (measured before occlusion), will be assessed in a fasted state, supine position, and under standardized conditions, as advised by the expert consensus of Thijssen *et al.* [57]. Offline analyses of the pseudonymized images of the two centres will be performed by one expert, blinded for the randomization arm.

In a subgroup of participants recruited at University Hospitals Leuven, dynamic vessel analysis of the retinal microvasculature (Dynamic Vessel Analyzer, Imedos GmbH, Jena, Germany) will be used to assess endothelial function of the small blood vessels. The details of the assessment procedure have been described elsewhere [58, 59]. Dynamic vessel analysis will not be performed in participants with an anterior chamber depth of <25% of the corneal thickness [60].

##### Quality of life

The Short Form Health Survey (SF-36) is a self-report instrument that will be used to measure limitations in physical, social, and role activities due to poor health and/or bodily pain. It consists of eight categories: physical functioning, role limitations due to physical health, body pain, general health, vitality, social functioning, role limitations due to emotional health, and mental health. These categories are summarized into a physical component score and a mental component score. The ‘Impact on Participation and Autonomy’ questionnaire will be used to measure participants’ ability to participate in activities and make decisions for themselves. It is a valid, reliable, and acceptable measure of participation and autonomy [61]. In-depth semi-structured interviews will be conducted in 29 participants from Ghent University Hospital to explore their experiences with role management and participation during their rehabilitation process. The interviews will be recorded and transcribed. The transcripts will be analysed using Nvivo software to gain insight into the participants’ experiences.

##### Physical activity

Physical activity will be measured using two methods: accelerometery and self-reporting questionnaires. Accelerometery entails wearing an Actigraph wGT3X-BT device at the waist for 7 days to estimate time spent at light, moderate, and vigorous intensity [62]. Participants will be instructed to wear the Actigraph continuously from waking until bedtime for seven consecutive days, immediately starting after completion of the test day. Self-reported physical activity will be measured using the Physical Activity Vital Sign questionnaire, which asks about the days and minutes per week spent in moderate and vigorous physical activity [46].

Perceived barriers and facilitators to physical activity will be measured using the Motivators and Barriers Questionnaire [47]. This questionnaire lists various barriers and facilitators to physical activity and asks the respondent to rate their level of agreement with each item on a four-point scale (from ‘not at all’ to ‘very much’).

##### Safety

An independent Safety and Monitoring Committee will be un-blinded to the randomization groups, monitoring (serious) adverse events during the exercise intervention. Throughout the duration of the study, all participants will be asked to complete a self-developed questionnaire evaluating adverse events and the Immune Status Questionnaire on a monthly basis and at the pre-defined follow-up timepoints to prospectively assess infection incidence and other potential adverse events/reactions [63]. The questionnaire encompasses questions related to infection, hospitalization, musculoskeletal pain, or dysfunction, and hypoglycaemic or cardiorespiratory events. Objectively diagnosed infections for which the study participants sought medical care will be monitored. In addition, long-term graft survival and mortality will be monitored for up to 10 years after inclusion in the study.

### Statistical considerations

#### Sample size calculation

To determine the alpha level, a hierarchy in the hypothesis tests was specified; the comparison of MHIT *vs.* CON will be tested at an alpha level of 0.05. If the previous test was significant, the comparisons of MIT *vs.* CON and MHIT *vs.* MIT will be tested at an alpha level of 0.025. A difference of 2.5 ml·kg^−^^1^·min^−^^1^ in VO_2_peak is considered the minimum clinically important difference [64]. Based on a two-sided analysis of covariance, comparing the mean at the post-intervention time point and correcting for the baseline level of VO_2_peak, a total sample size of 123 is required to have 80% power to detect a difference of 2.5 ml·kg^−^^1^·min^−^^1^ in VO_2_peak between CON and MHIT after the 6-month training intervention (T3). This calculation assumes a standard deviation of 5.0 ml·kg^−^^1^·min^−^^1^ and a 0.7 Rho correlation between the baseline and post-training VO_2_peak levels, based on unpublished data from 20 *de novo* heart transplant recipients from the University Hospitals Leuven. To account for an anticipated dropout rate of 15%, a total of 147 KTRs will be recruited for the present study. If the actual dropout rate exceeds this estimate, additional recruitment will be considered.

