#### Statistical analyses

The full analysis set will include all randomized participants and will be used to evaluate all efficacy and safety endpoints according to the intention-to-treat principle. The per protocol set will exclude participants with major protocol deviations and will be reviewed and finalized at a Blind Review Meeting before the database is locked. Only patients with 70% adherence to the prescribed aerobic training sessions will be included in the per protocol analysis. Moreover, before final assessment, patients have to exercise for two consecutive weeks. Participants who do not fulfil these requirements will not be included in the per protocol analysis.

The sample size calculation was based on an analysis of covariance, but a constrained longitudinal data analysis will be used to evaluate the difference in VO_2_peak, taking into account the potential for missing values [65]. The model will be fit to all longitudinal data and will include a fixed effect for centre and sex. Pairwise comparisons between treatment groups will be made using a predetermined hierarchy and will be tested at different alpha levels depending on the comparison being made. The comparison MHIT group *vs.* CON group is first tested at 0.05 and—if this test is significant—the comparisons MIT group *vs.* CON group and MHIT group *vs.* MIT group at 0.025 alpha level.

For continuous secondary outcomes measured longitudinally, the same approach will be used as for the primary outcome, which is a constrained longitudinal data analysis model. For binary secondary outcomes measured longitudinally, a generalized linear mixed model will be applied. The alpha level for testing the significance will be set at 0.05.

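### Halving alpha to 0.025 for MIT vs CON and MHIT vs MIT is unnecessary: after MHIT vs CON is rejected, both can be tested at 0.05 without raising the family-wise error ceiling

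*Protocol article*

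**What the plan says.** The rule appears twice in the Protocol article, and the two statements agree.

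- Under *Sample size calculation*, the first comparison is MHIT vs CON: "CON will be tested at an alpha level of 0.05". The other two are conditional on it ("If the previous test was significant, the comparisons of MIT" vs CON, and MHIT vs MIT), and the level drops: "MIT will be tested at an alpha level of 0.025".
- Under *Statistical analyses*, the same order and levels are repeated for the constrained longitudinal model, ending "MIT group at 0.025 alpha level".

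The only reason given is that a hierarchy was specified. The Abstract names the two conditional comparisons as the secondary hypotheses on VO2peak after the 6-month programme.

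**The concern.** Splitting alpha in two is the usual Bonferroni step when two null hypotheses can be true together. Here they cannot both be true once MHIT and CON differ, because the three pairwise nulls are linked: MIT = CON together with MHIT = MIT implies MHIT = CON. The plan therefore pays for a multiplicity problem that its own first test has removed.

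The comparisons that pay are MIT vs CON and MHIT vs MIT. The second is the direct test of training intensity, which the Abstract's conclusion and the Discussion present as the question the trial addresses. Both already have less power than MHIT vs CON, because they carry a stricter level and are tested only if the first test succeeds.

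**Working it through.** **Inputs (all from *Sample size calculation*, except allocation from *Randomization and blinding*).** Two-sided test ("Based on a two-sided analysis of covariance"); effect ("A difference of 2.5 ml", in ml/kg/min); SD ("This calculation assumes a standard deviation of 5.0"); correlation ("a 0.7 Rho correlation between the baseline and post-training"); 123 evaluable in three equal arms, so 41 per arm; 15% dropout; 147 recruited.

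**Step 1. Reproduce the plan's sample size.**

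Residual SD after baseline adjustment = 5.0 × √(1 − 0.7²) = 3.571.

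Per-arm n (normal approximation) = 2 × [3.571 × (z for alpha + 0.8416) / 2.5]².

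- Alpha 0.025: z = 2.241, n = 38.8, so 39 per arm. The t calculation with 2n − 3 degrees of freedom gives 41 per arm = **123**.
- Alpha 0.05: z = 1.960, n = 32.0 (just above), so 33 per arm. The t calculation gives 34. The total is 99 to 102.

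Dropout: 41 / 0.85 = 48.2, so 49 per arm = **147**.

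The stated total is thus reproduced at alpha 0.025, although the text attaches it to MHIT vs CON, which is tested at 0.05.

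**Step 2. Family-wise error by logic, with follow-on tests at 0.05.**

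- *MHIT = CON is true.* No follow-on test is made unless this true null is first rejected, which has probability at most 0.05. Any family-wise error lies inside that event, whatever level the follow-on tests use.
- *MHIT = CON is false.* MIT = CON and MHIT = MIT cannot both be true. At most one true null remains, tested once at 0.05, so the error is at most 0.05.

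These cases cover everything. The argument uses only the relation between the hypotheses, so it applies equally to contrasts from the planned constrained longitudinal model.

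**Step 3. Family-wise error by simulation.** Three arms of 41, residual SD 3.571, pooled t with 3 × 41 − 4 = 119 degrees of freedom, 2,000,000 runs per scenario.

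| True state | Follow-on at 0.025 | Follow-on at 0.05 |
|---|---|---|
| All equal | 0.050 | 0.050 |
| MHIT = CON, MIT +2.5 | 0.050 | 0.050 |
| MHIT = CON, MIT +10 | 0.050 | 0.050 |
| MIT = CON, MHIT +2.5 | 0.019 | 0.038 |
| MIT = MHIT = CON +2.5 | 0.019 | 0.038 |
| MIT = CON, MHIT +10 | 0.025 | 0.050 |
| MIT = MHIT = CON +10 | 0.025 | 0.050 |

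The maximum is 0.05 in both columns. Counting wrong-direction rejections as errors does not change this.

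**Step 4. Power.**

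Standard error of a difference = 3.571 × √(2/41) = 0.789.

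- *True difference 2.5, one comparison, ignoring the first test.* 2.5 / 0.789 = 3.170. At 0.025: Φ(3.170 − 2.241) = 82.3%. At 0.05: Φ(3.170 − 1.960) = 88.7%. With the two-arm t: 81.0% and 87.9%.
- *True difference 2.5, first test included, MHIT 2.5 above CON and MIT equal to one of them (simulated).* Power for the comparison with a real difference is 75% at 0.025 and 81% at 0.05.
- *True difference 1.25 for MHIT vs MIT, ignoring the first test.* 1.25 / 0.789 = 1.585. At 0.025: Φ(1.585 − 2.241) = 25.6%. At 0.05: Φ(1.585 − 1.960) = 35.4%. With the first test included and MHIT 2.5 above CON (simulated): 24.6% and 34.0%.

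**The case against.** The strongest reply is that nothing here is wrong. The rule is prespecified, stated consistently and controls family-wise error; a sharper procedure is a preference. It is true that the rule is valid. But the efficiency is lost without lowering the ceiling the plan has set for itself.

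It can also be said that the split does reduce false positives. When MHIT truly differs from CON and one null remains true, the table shows the error halved. That is correct. However, the plan accepts 0.05 for the first test, and its maximum family-wise error is 0.05 either way. The lower figures in those scenarios are unused allowance.

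Third, a total of 123 is what alpha 0.025 requires, so the trial may have been sized to give the follow-on comparisons 80% power. The protocol does not say so. Even if it was, the same participants yield more power at 0.05.

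Three points stand in part:

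- The 1.25 scenario is half the protocol's minimum important difference and is an illustration, not a planning value. MHIT vs MIT remains poorly powered there at either level.
- The Introduction says only that the role of intensity will be explored, so how much weight these comparisons carry is open to reading.
- Loosening a published threshold needs a documented amendment, and the sample-size text must be made to match.

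**Conclusion.** The point holds. The step down to 0.025 is valid but unnecessary; testing both follow-on comparisons at 0.05 keeps strong family-wise control at 0.05. The cost of the present rule is about 7 percentage points of power per comparison at a difference of 2.5 (81% against 88%), about 5 to 6 points when the first test is included (75% against 81%), and roughly 10 points for an MHIT vs MIT difference of 1.25.

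The error-control result is exact and does not depend on the SD or correlation. The power figures assume SD 5.0, correlation 0.7 and 41 evaluable per arm. The argument covers only the three pairwise VO2peak contrasts at T3. It does not extend to other visits or endpoints.

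**What to change.** In both *Sample size calculation* and *Statistical analyses*, replace 0.025 by 0.05 for MIT vs CON and MHIT vs MIT, still tested only if MHIT vs CON is significant at 0.05. Add a sentence such as: *For VO2peak at T3 this is a closed testing procedure; because the three pairwise null hypotheses are logically related, strong family-wise error control at 0.05 is preserved.*

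At the same time, correct the sample-size statement. Say that 123 was obtained at two-sided alpha 0.025, if the sponsor confirms this, and that at 0.05 the same 41 per arm gives about 88% power for a difference of 2.5. Recruitment of 147 can stay as planned.

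The change should be a dated amendment made while treatment-group results are still blinded, with the registry record and any analysis plan brought into line. It needs no extra participants, visits or data, and leaves the family-wise error ceiling at 0.05.

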### Randomization and blinding

Participants will be randomized on an allocation ratio of 1:1:1 to either 6 months of home-based moderate-intensity training followed by a physical activity intervention (MIT; *n* = 49); 6 months of home-based training combining 3 months of moderate and 3 months of high intensity followed by a physical activity intervention (MHIT, *n* = 49); or 6 months of home-based sham exercise training (CON; *n* = 49). A computer-generated randomization sequence, stratified for sex and study centre, will be developed and uploaded to a secure web application (REDCap) used for randomization and data management. Prior to randomization, participants will be clearly informed about the content of each possible intervention arm, including the stipulation that switching groups is not allowed and that adherence to the prescribed training programme is essential throughout the study. Outcome assessors and data investigators will be blinded to the participants’ group allocation, both in University Hospitals Leuven and Ghent University Hospital.

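### The stated total of 123 for 80% power on MHIT vs CON does not follow from the stated inputs, which need 99 to 102; 41 per arm gives about 88% power

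*Protocol article*

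**What the plan says.** All the inputs are printed in the protocol article, nearly all of them under Sample size calculation.

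- **Alpha.** For the first comparison, MHIT vs "CON will be tested at an alpha level of 0.05". If that test is significant, MIT vs CON and MHIT vs "MIT will be tested at an alpha level of 0.025". The Statistical analyses section repeats both levels.
- **Method.** "Based on a two-sided analysis of covariance, comparing the mean at the post-intervention time point and correcting for the baseline level" of VO2peak.
- **Requirement.** "a total sample size of 123 is required to have 80% power to detect a difference of 2.5" ml/kg/min, "between CON and MHIT after the 6-month training intervention (T3").
- **Variability.** "This calculation assumes a standard deviation of 5.0" ml/kg/min and "a 0.7 Rho correlation between the baseline and post-training VO_2_peak levels".
- **Allocation.** Under Randomization and blinding: "Participants will be randomized on an allocation ratio of 1:1:1". So 123 means 41 per arm.
- **Dropout.** 15%, leading to 147 recruited (49 per arm).

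**The concern.** The paragraph ties one comparison (MHIT vs CON), one alpha (0.05), one power (80%) and one total (123) together. Anyone who puts the printed inputs through the named method gets a smaller total. The gap is 21 to 24 participants, too large for rounding or for the choice between a normal and a t calculation.

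This is the only power statement in the article, and it concerns the primary endpoint. As printed, it understates the power of the primary test and leaves the basis of the sample size unclear. It does not put the primary comparison at risk: the discrepancy runs in the safe direction.

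**Working it through.** **Inputs** (all from Sample size calculation, except the 1:1:1 allocation): difference d = 2.5, SD = 5.0, rho = 0.7, power 80%, two-sided alpha 0.05 for MHIT vs CON and 0.025 for the follow-on comparisons.

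**Step 1. Residual SD under ANCOVA.** s = 5.0 × sqrt(1 − 0.7²) = 5.0 × sqrt(0.51) = 3.571, so s² = 12.75.

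**Step 2. Trying to reproduce 123 at the stated alpha of 0.05.**
Normal approximation: n per arm = 2 × (1.960 + 0.842)² × 12.75 / 2.5² = 32.0 (32.02 unrounded), so 33 per arm and 99 in total.
Noncentral t, with noncentrality d / (s × sqrt(2/n)):
- pairwise error df 2n − 3: power is 79.97% at n = 33 and 81.2% at n = 34, so 34 per arm and 102 in total;
- three-arm error df 3n − 4: power is 80.4% at n = 33, so 33 per arm and 99 in total.

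The stated figure is 41 per arm and 123 in total. It is not reproduced.

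**Step 3. Power that 41 per arm gives at 0.05.** Noncentrality = 2.5 / (3.571 × sqrt(2/41)) = 2.5 / 0.789 = 3.17. Power is 87.9% (df 2n − 3), 88.2% (df 3n − 4) or 88.7% (normal), so about 88% against the stated 80%.

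**Step 4. The dropout step.** 41 / 0.85 = 48.2, rounded up to 49; 49 × 3 = 147. This reproduces, so the mismatch lies before it. The same step from the recomputed requirement gives 33 / 0.85 = 38.8, so 39 × 3 = 117, and 34 / 0.85 = 40, so 40 × 3 = 120.

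**Step 5. What could have produced 123.**

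| Calculation (80% power unless noted) | Total over three arms |
|---|---|
| Two-sided 0.05, ANCOVA as stated | 99 to 102 |
| One-sided 0.05, ANCOVA | 78 |
| Two-sided 0.05, change score | 114 |
| Two-sided 0.05, post-training value only | 189 |
| Two-sided 0.05, ANCOVA, 85% power | 111 |
| Two-sided 0.05, ANCOVA, 90% power | 129 |
| Two-sided 0.025, ANCOVA, normal | 117 |
| Two-sided 0.025, ANCOVA, t with df 3n − 4 | 120 |
| Two-sided 0.025, ANCOVA, t with df 2n − 3 | **123** |
| Three-group F test at 0.05, means 0, 1.25, 2.5 | **123** |

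Reading 123 as a two-arm total (61.5 per arm) gives 97% power, so that does not explain it either. At 0.025 with df 2n − 3, power is 79.9% at 40 per arm and 81.0% at 41, so 41 is the exact minimum.

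**Step 6. Follow-on comparisons at 41 per arm, gate included.** The simulation uses normal residuals with SD 3.571, requires MHIT vs CON to be significant at 0.05, and then tests each follow-on comparison at two-sided 0.025. MHIT is 2.5 above CON in both rows.

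| Position of MIT | MIT vs CON | MHIT vs MIT |
|---|---|---|
| Equal to MHIT (2.5 above CON) | about 75% | about 2% |
| Midway (1.25 above CON) | about 25% | about 25% |

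The ungated figure of 81% applies to a follow-on comparison whose own true difference is 2.5. It can hold for both follow-on comparisons only if MHIT is 2.5 + 2.5 = 5.0 above CON, twice the difference used for sizing.

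**The case against.** The strongest reply is that nothing is harmed. The primary comparison has more power than claimed, the dropout inflation is right, and no test, alpha level, test order or enrolment figure changes. A power of at least 80% for MHIT vs CON is true. All of that stands, and it limits the weight of the point to a wrong figure that is cheap to correct. It does not make the printed requirement follow from the printed inputs, and an unseen analysis plan cannot account for the gap because every input is given here.

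Four stronger readings are tempting and are not supported.

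- **That 123 can only have come from alpha 0.025, so that the follow-on comparisons drove the size.** This is inference. The match at 0.025 depends on pairwise error df; three-arm df gives 120. An omnibus F test at 0.05 with MIT midway also gives 123, although the article describes neither that test nor that assumption.
- **That the trial is underpowered for its primary test.** The opposite is true.
- **That decisions on extra recruitment will be judged against a wrong power benchmark.** The article ties extra recruitment to dropout above its 15% estimate, not to a power figure.
- **That the article is at fault for giving no power for MIT vs CON or MHIT vs MIT.** The abstract presents these as secondary hypotheses, and a condensed article may leave their power to the full protocol.

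**Conclusion.** The point holds as an arithmetic error in the primary power statement. The printed inputs require 33 to 34 evaluable participants per arm (99 to 102 in total), not 41 (123). At 41 per arm the power for MHIT vs CON is about 88%, some 8 percentage points above the stated 80%. Alpha 0.025 is a likely source of 123 but is not documented as such.

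The conclusion takes the article's own SD, correlation and difference at face value, assumes equal arms and a pairwise ANCOVA on the T3 value, and does not depend on whether a normal or a t calculation is used. It concerns the sizing calculation as described. The planned constrained longitudinal model is a separate matter, which the article itself distinguishes from the sizing method.

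**What to change.** Keep 147 and correct the text under Sample size calculation:

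1. State the alpha, the test and the error degrees of freedom that produced 123. If 0.025 was used to size the trial, say so and for which comparison. If another method was used, name it and its assumptions.
2. Restate the primary power: 41 evaluable participants per arm give about 88% power for MHIT vs CON at two-sided 0.05 for a true difference of 2.5 ml/kg/min, with SD 5.0 and rho 0.7.
3. If power is given for the follow-on comparisons at 0.025, state the three assumed means and include the gate: for example, about 75% for MIT vs CON if MIT and MHIT are both 2.5 above CON. Do not print 81% for both follow-on comparisons beside 88% for MHIT vs CON at a difference of 2.5, because no single set of means gives all three.

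The cost is a few sentences. Enrolment, randomisation, alpha levels and the analysis are unchanged.
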